Because of the absence of preliminary clinical results in the literature about donepezil and CIPN, and the recommendations of international experts (expertise of our project in the framework of a call for projects), we will perform a proof-of concept study to generate preliminary results for a future randomised placebo-controlled phase 3 study if the results are positive. Then, for the primary endpoint, the responder rate will not be compared to placebo, but assessed only for the donepezil arm after 16 weeks of treatment. Donepezil will be considered effective if 7 or more responders are observed in the 33 patients of the donepezil arm (see “statistics” paragraph for details). The responder rate will be compared to the placebo arm only for the secondary endpoint.

In the event of a beneficial therapeutic effect at the end of treatment (significant reduction in neuropathic disorders [reduction of one grade of neuropathy (according to NCI-CTCAE v4.0 or QLQ-CIPN20 score) or -30% of neuropathic pain (according to NRS 0–10 scale), if present, or PGIC score of 6 or 7]), the investigator will be allowed to request a lifting of the treatment blind, to adapt the further management of the patient and/or refer the patient to a specialist (neurologist, pain physician).

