#### Secondary endpoints

The evolution of all the secondary parameters will be studied in an intragroup (before *vs.* after treatment) and an intergroup (placebo *vs.* donepezil arm): i) Sensory, motor and autonomic scales from the QLQ-CIPN20 questionnaire (see below); ii) Grading of OIPN by NCI-CTCAE v4.0: this scale will be used to grade the severity of sensory neuropathy from 1 to 4 (1 = Asymptomatic, 2 = Moderate symptoms; limiting instrumental of Activities of Daily Living [ADL], 3 = Severe symptoms; limiting self-care ADL, 4 = Life-threatening consequences; urgent intervention indicated); iii) Assessment of neuropathic pain: monthly assessment of pain felt in the last week by 11-point NRS. This scale is used for adults and children 10 years old or older patient self-reporting of pain (score of 0 = no pain and 10 = worst possible pain). If NRS ≥ 4/10, neuropathic pain will be validated by the DN4 interview questionnaire (“*Douleur Neuropathique 4*”) will be mandatory. The interview portion of the DN4 questionnaire is a clinician-administered screening tool for neuropathic pain [59]. The questionnaire includes 7 items (YES or NO, the test is positive for a score ≥ 3/7). If the patient have a positive DN4 and a pain intensity ≥ 4/10 (NRS), neuropathic pain will be confirmed and will be characterized by the Neuropathic Pain Symptom Inventory (NPSI) questionnaire. This self-reported questionnaire assesses neuropathic pain symptoms [60], and includes 12 items; iv) HRQoL by the QLQ-C30 questionnaire (EORTC): this auto-questionnaire (EORTC) assesses the HRQoL of cancer patients, and includes five functional scales, three symptom scales, an overall HRQoL scale, and a number of additional elements assessing other symptoms; v) Anxiety and depression by the hospital anxiety and depression scale (HADS) questionnaire: this auto-questionnaire detects anxiety and depressive disorders, and includes 14 items rated from 0 to 3 (7 questions for anxiety and 7 for depression). The following interpretation is proposed for each of the two total scores: ≤ 7: absence of symptomatology; 8 to 10: suggestive symptomatology; ≥ 11: indicative symptomatology; vi) Patients’ Global Impression of Change (PGIC): PGIC [61] assesses the general effectiveness of the treatment according to the impression of patient, with the scores from 1 to 7 (from aggravated to very improve); vii) Safety: the time to treatment failure will be assess. This is the interval between randomization to treatment discontinuation for any reason. The assessment of adverse events (AEs) associated with study treatment will be also assessed by NCI-CTCAE v4.0. Any AEs will be collected daily by the patient and during the monthly visits. AEs will be categorized according to their intensity, treatment-related or not and by type. At last, viii) Assessment of painkiller consumption (if any): drug consumption for OIPN will be assessed throughout the study.

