#### Statistical analysis

All statistical analyses will be performed using SAS software version 9.4 before breaking the randomization codes, according to International Conference on Harmonization-Good Clinical Practice guidelines. A two-sided *p*-value of less than 0.05 will be considered for the statistical significance of all the analyses. The results will be expressed as hazard-ratios and 95% confidence intervals. Secondary analyses will be exploratory.

The baseline description of the patients included in the analysis will be carried out, without presenting inferential statistical tests (according to recommendations). As part of a proof-of-concept, only patients who have completed the study (treatment received in its entirety for 16 weeks whatever the dose = per protocol population) will be analyzed for the primary endpoint. The primary endpoint will be the rate of responders and will be described using frequency and percentage. A 95% one-sided confidence interval will also be calculated. Subgroup analyses for the primary endpoint will be planned for each stratum of the randomization (neuropathy grade, age of neuropathy and type of chemotherapy).

For the secondary endpoints, analyses will be performed on the intention-to-treat and per-protocol populations and compared to the placebo arm.

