Descriptive statistics will be presented by treatment arms. Continuous variables will be presented as mean and standard deviation (otherwise as median and interquartile range) and will be compared between arms using the unpaired t test or the Mann–Whitney U test when appropriate according to the assumptions of the t-test: (i) the Shapiro–Wilk test will be used to assess normality, and (ii) the Fisher-Snedecor test to assess homoscedasticity. When appropriate (for example, for the sensory scores of the QLQ-CIPN20), these analyses will be supplemented by the recommendations proposed by Vickers and Altman, i.e. ANCOVA, considering baseline scores as covariates. Then, multiple linear mixed models could be run with centers as random-effects. Covariates will be determined according to univariate results and to their clinical relevance, including stratification parameters. The normality of residuals will be studied as described previously. If appropriate, a transformation (for example logarithmic) should be proposed to achieve the normality of dependent variable. The results will be expressed as regression coefficients and 95% confidence intervals. The analyses of other continuous secondary endpoints (11-point pain NRS, DN4 interview, NPSI, HADS and QLQ-C30 questionnaires) will be carried out similarly. For categorical parameters (adverse effects, PGIC, DN4 interview or HADS categorized according to literature), Chi-squared or Fischer exact tests will be used to compare the treatment arms. A generalized linear mixed model (more precisely logistic regression for dichotomous outcomes) will be applied for multivariable analyses. The results will be expressed as relative risks and 95% confidence intervals.

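### PGIC, an ordered 1-to-7 score, is compared between arms only by chi-squared or Fisher tests, which ignore its order and give away power that a rank test would keep

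*Protocol article*

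**What the plan says.** The Secondary endpoints section says that PGIC "assesses the general effectiveness of the treatment according to the impression of patient, with the scores from 1 to 7", running from worse at the low end to much better at the high end. It is therefore an ordered scale.

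The Statistical analysis section then assigns tests by type of variable:

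- **Continuous variables:** t test or Mann-Whitney, with ANCOVA and mixed models where suitable. The other continuous endpoints named for this treatment are pain NRS, DN4 interview, NPSI, HADS and QLQ-C30. PGIC is not among them.
- **Categorical variables:** "For categorical parameters (adverse effects, PGIC, DN4 interview or HADS categorized according to literature), Chi-squared or Fischer exact tests will be used" to compare the arms. PGIC appears here and in no other list.
- **Multivariable analysis of categorical outcomes:** "A generalized linear mixed model (more precisely logistic regression for dichotomous outcomes) will be applied for multivariable analyses". Results are to be given as relative risks. No ordinal model is named.

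The section on the primary endpoint mentions a cut on this scale, "or PGIC score of 6 or 7", but as one criterion for asking to lift the blind after treatment. It does not define an analysis variable.

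The significance level is a two-sided p-value "of less than 0.05 will be considered for the statistical significance of all the analyses", and the same section says: "Secondary analyses will be exploratory".

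**The concern.** A treatment that helps should move patients up the PGIC scale. A chi-squared test on seven levels looks for any difference in the distribution, in any pattern, and spends 6 degrees of freedom on it. A rank test spends one degree of freedom on the direction that matters. If PGIC is first split into two groups, the order within each group is discarded instead.

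This is a stated choice of method, not a detail left open. DN4 and HADS get both a score-based and a categorised analysis, whereas PGIC gets only the kind that ignores order.

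The stakes are modest but real. The primary endpoint is judged in the donepezil arm alone, so every placebo-controlled comparison is secondary, and PGIC is one of those listed in the Study objectives. With 33 to 40 patients per arm, an inefficient test can miss a benefit that patients themselves report. A seven-level chi-squared test also gives no single effect estimate to carry forward.

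**Working it through.** **Step 1. The plan's own figure.** The article states no power for PGIC. Its only design calculation is for the primary rule, at least 7 responders of 33, with p0 = 10% and p1 = 30%. Exact binomial: P(X ≥ 7 | 33, 0.10) = 0.0417 and P(X ≥ 7 | 33, 0.30) = 0.9056. Both agree with the stated 0.0417 and 91%. This rule does not involve PGIC.

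**Step 2. Why degrees of freedom matter.** The 5% critical value of chi-squared is 3.84 on 1 df and 12.59 on 6 df. If a 1-df ordinal test has 80% power, its noncentrality is about 7.85. If the 6-df test has the same noncentrality, its power is 52%, a relative loss of 1 − 52/80 = 35%. The loss changes with the starting power:

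| Power of ordinal test | Power of 6-df chi-squared | Relative loss |
|---|---|---|
| 50% | 26% | 48% |
| 70% | 41% | 41% |
| 80% | 52% | 35% |
| 90% | 67% | 26% |
| 95% | 78% | 18% |

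**Step 3. A worked scenario.** From the article: 33 evaluable or 40 randomised per arm, two-sided 0.05. Assumed, because the article gives neither: placebo distribution over levels 1 to 7 of 3/7/15/40/20/10/5%, and a donepezil shift of 0.6 or 0.7 SD on an underlying normal scale.

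The placebo share scoring 6-7 is 10% + 5% = 15%, so the cut lies at z = 1.036. After the shift the share is 1 − Φ(1.036 − 0.6) = 33.1% or 1 − Φ(1.036 − 0.7) = 36.8%.

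Simulated power:

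| Test | 33 per arm, 0.6 SD | 33 per arm, 0.7 SD | 40 per arm, 0.6 SD | 40 per arm, 0.7 SD |
|---|---|---|---|---|
| Chi-squared, 7 levels | 29% | 42% | 37% | 52% |
| Chi-squared (uncorrected), 6-7 v 1-5 | 43% | 56% | 50% | 62% |
| Fisher, 6-7 v 1-5 | 29% | 43% | 40% | 53% |
| Mann-Whitney | 63% | 77% | 71% | 84% |

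Exact enumeration of the two split tests at 33 per arm gives 42% and 55% (chi-squared) and 30% and 42% (Fisher), within about a point of the table.

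Relative loss against Mann-Whitney at 33 per arm (0.6 SD, then 0.7 SD):

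- Seven-level chi-squared: 1 − 29/63 = 54%; 1 − 42/77 = 45%.
- Split, chi-squared: 1 − 43/63 = 32%; 1 − 56/77 = 27%.
- Split, Fisher: 1 − 29/63 = 54%; 1 − 43/77 = 44%.

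**Step 4. Other assumptions.** Four assumed seven-level distributions with proportional-odds shifts (odds ratio 2 to 5) at 33 and 40 per arm gave a relative loss of 13% to 62% for seven-level chi-squared. For a 6-7 split it was about 4% to 41% with uncorrected chi-squared and about 6% to 64% with Fisher. The rank test had the higher power in every one of these scenarios.

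**The case against.** **The seven-level reading is not certain.** The words about categorising according to the literature may cover PGIC as well as HADS. Logistic regression for dichotomous outcomes and relative risks fit a binary PGIC better than seven unordered levels. This stands as a doubt about the text, and it matters for size. At 15% v 37% with 33 per arm, the smallest expected count is 33 × (0.15 + 0.37)/2 ≈ 8.6, so by the usual rule chi-squared would be used rather than Fisher, and the loss is smaller. It does not remove the point: the rank test still has more power, and no cut-off for analysis is stated.

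**A single headline loss is tempting.** A reader might infer that the plan gives up about a third of the available power. The article does not support that as a property of the plan, since it states no PGIC distribution or effect. A relative loss near a third for the seven-level test appears only when the ordinal test would have about 80-87% power.

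**The consequence is limited.** A reader might also infer that the phase 3 decision loses its controlled evidence. It does not. Secondary analyses are exploratory and the proof-of-concept decision rests on 7 of 33 responders. QLQ-CIPN20 scores are compared with placebo by ANCOVA and mixed models, and several other scores by t test or rank methods.

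**The tests are valid.** Chi-squared and Fisher control the type I error, a responder split is easy to read, and a generalised linear mixed model could include a cumulative-logit form. All true, but the article specifies the logistic form for dichotomous outcomes and names no ordinal one. The proportional-odds assumption would also be hard to check with 33 per arm and sparse end categories, which is why that model should be optional.

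**Conclusion.** The point holds as a minor one. The article assigns an ordered seven-level score only to tests that ignore order, while comparable scores also get an analysis that uses it. The ordinal comparison has more power whether PGIC is tested on seven levels or split at 6-7.

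The size is conditional on the assumptions in Step 3. Under them, Mann-Whitney exceeds the seven-level chi-squared by 32 to 35 percentage points and a 6-7 split tested by chi-squared by 20 to 22 points, across both sample sizes. Other distributions and effects give smaller or larger gaps, so any figure should be quoted as a range with its assumptions. The primary endpoint, the sample size and the go/no-go rule are untouched.

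**What to change.** In the Statistical analysis section, take PGIC out of the list of categorical parameters and state that:

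- the seven ordered levels are compared between arms by the Mann-Whitney test with tie correction;
- optionally, a proportional-odds model gives a common odds ratio with 95% confidence interval, with the note that its assumption can be checked only weakly at this size;
- the proportion scoring 6 or 7 is reported by arm as a descriptive summary, with the cut fixed in advance.

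The change is one or two sentences. It needs no new data, patients or software, since Mann-Whitney is already in the plan. It should be made before the data are unblinded.

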#### Inclusion/randomization visit (V0)

The study will be presented to the patient, along with the objectives, organization, constraints, and assessment questionnaires. If the patient accepts to participate, they will confirm it by signing the informed consent form prior to any study procedure. The following will be performed:Validation of patient eligibility (inclusion and non-inclusion criteria),Clinical examination and body weight,Electrocardiogram and heart rate,Blood sampling (hepatic and renal function, complete blood count),Verification of presence of OPIN (QLQ-CIPN20),Randomization,Completion of study questionnaires (HADS and QLQ-C30),Neuropathic pain assessment: 11-point NRS, and if pain score ≥ 4 / 10 then perform DN4 interview and complete NPSI questionnaire if DN4 interview positive (score ≥ 3 / 7),Assessment of painkiller consumption (if applicable),Delivery of study treatment according to randomization for a 4-week period: donepezil or placebo.

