Repeated data collected longitudinally will be analyzed by mixed models (linear or generalized linear according to dependent variable) to study the following fixed effects, arm, time and their interaction taking into account between and within patient variability (patient as random-effect, in addition to center effect) [62]. Particular attention will be paid to safety analysis (by group: type, intensity, frequency of adverse effects). Exit rates due to adverse effects will be considered as a censored data. These criteria will be estimated by the Kaplan–Meier method, compared between groups by the log-rank test, and investigated in a multivariate marginal Cox model considering center effects. The proportional-hazard hypothesis will be verified using Schoenfeld’s test and plotting residuals. Finally, to put significant results in perspective, a sensitivity analysis will be conducted to measure the impact of the missing data. A worst-case scenario will be defined as one where patients with missing data do not react to the treatment (whatever the treatment may be). Additional analyses will then be performed according to the statistical nature of missing data (missing at random or not), in particular multiple imputation or estimations proposed by Verbeke and Molenberghs [63] adapted specifically to repeated data.

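### The longitudinal donepezil-placebo models are specified by arm, time and arm x time, without the baseline and strata adjustment that the plan makes only conditional elsewhere, so their week-16 contrast is less precise than it need be

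*Protocol article*

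**What the plan says.** All of this is in the protocol article under Statistical analysis, unless noted.

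- **Longitudinal models.** Repeated data go into linear or generalized linear mixed models "to study the following fixed effects, arm, time and their interaction taking into account between and within patient variability". The random part is "patient as random-effect, in addition to center effect". No covariate is named, and the role of V0 is not stated.
- **Comparison of continuous endpoints, described just before.** Unpaired tests come first. Then, where appropriate and with the QLQ-CIPN20 sensory score as the example, "these analyses will be supplemented by the recommendations proposed by Vickers and Altman, i.e. ANCOVA, considering baseline scores as covariates". The text continues: "Then, multiple linear mixed models could be run with centers as random-effects". On covariates: "Covariates will be determined according to univariate results and to their clinical relevance, including stratification parameters". On the remaining scales: "The analyses of other continuous secondary endpoints (11-point pain NRS, DN4 interview, NPSI, HADS and QLQ-C30 questionnaires) will be carried out similarly".
- **Strata.** Subgroup analyses are planned for "each stratum of the randomization (neuropathy grade, age of neuropathy and type of chemotherapy", so there are three stratification factors.
- **Data available.** The V0 visit includes "Verification of presence of OPIN (QLQ-CIPN20" and the pain NRS. Both are repeated at V1 to V4 and at the follow-up call.
- **Status.** Secondary analyses, including the comparison with placebo, are declared exploratory. The primary endpoint is a responder count in the donepezil arm alone.

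**The concern.** The mixed model uses every visit for the comparison with placebo. The Discussion says this comparison will strengthen the evidence, and the trial is meant to prepare a phase 3 study. The comparison was not sized: 33 evaluable patients per arm come from the single-arm rule. Avoidable imprecision therefore matters more than usual.

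The authors endorse baseline adjustment in one paragraph and give the longitudinal model its own list of effects, without that adjustment, in the next. Run as listed, that model does not make the best use of the V0 score, although the score is collected on everyone. The adjustment offered elsewhere is optional and lets univariate results influence which covariates enter, so it does not fix one pre-specified adjusted estimate.

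**Working it through.** **The plan's own figure.** With 33 patients, a threshold of 7 responders, p0 = 10% and p1 = 30%, the exact binomial gives a type I error of 0.0417 and power of 0.9056. Both match the article (0.0417 and 91%). Neither depends on the mixed model. No precision or power is stated for the between-arm comparison.

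**Inputs.** n = 33 per arm (Sample size estimation). The correlation rho between baseline and week 16, the SD and the true difference are not in the document. They are assumptions here.

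**Variance of the week-16 arm contrast.** Take unit SD, equal correlation between visits and complete data. Then variance = f x 2/n, with:

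- V0 as a free time point (contrast of change): f = 2(1 - rho)
- V0 left out (post-treatment only): f = 1
- Baseline as covariate, or a common baseline mean across arms: f = 1 - rho^2

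The ratios to the adjusted variance are 2/(1 + rho) and 1/(1 - rho^2). Both exceed 1 for any rho between 0 and 1.

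| rho | SE, V0 free | SE, V0 out | SE, adjusted | Ratio, V0 free | Ratio, V0 out |
|---|---|---|---|---|---|
| 0.3 | 0.291 | 0.246 | 0.235 | 1.54 | 1.10 |
| 0.5 | 0.246 | 0.246 | 0.213 | 1.33 | 1.33 |
| 0.7 | 0.191 | 0.246 | 0.176 | 1.18 | 1.96 |
| 0.8 | 0.156 | 0.246 | 0.148 | 1.11 | 2.78 |

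Example at rho = 0.5: unadjusted SE = sqrt(1.0 x 2/33) = 0.246; adjusted SE = sqrt(0.75 x 2/33) = 0.213.

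**Power without the entry rule.** Two-sided 5%, noncentral t with 64 degrees of freedom, assumed difference 0.6 SD. At rho = 0.5, power is 67% for either unadjusted form and 79% adjusted.

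**Effect of the entry rule.** Patients need a sensory score of at least 30, which narrows the baseline range. Assume an underlying SD of 18, an underlying mean m of 35, 40 or 45, and a 10-point difference (10/18 = 0.556 SD). With a = (30 - m)/18 and lambda = phi(a)/(1 - Phi(a)), the baseline variance is multiplied by k = 1 - lambda(lambda - a). For m = 40: a = -0.556, lambda = 0.481, k = 1 - 0.481 x 1.037 = 0.501. For m = 35 and 45, k = 0.428 and 0.581. Then:

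- V0 free: f = (1 - rho)^2 k + (1 - rho^2)
- V0 out: f = rho^2 k + (1 - rho^2)
- Adjusted: f = 1 - rho^2

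At underlying rho = 0.5, both unadjusted factors are 0.857, 0.875 and 0.895 (m = 35, 40, 45) against 0.75. Power is 67.0%, 66.1% and 65.1% against 72.8%, a gain of about 6 to 8 points. At rho = 0.7 the gain is about 2 to 3 points over the change contrast and 13 to 17 over the post-only contrast.

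**Strata.** A main effect of a stratum is constant over time, so with complete data it cancels from a V4 minus V0 contrast. At rho = 0.5, with a balanced stratum assumed to explain half of the between-patient variance, the SE with V0 free is 0.246 with or without the stratum. With V0 left out it falls from 0.246 to 0.213. Neuropathy grade is a banding of the sensory score (Study endpoints), so much of its gain overlaps with that of the continuous baseline. The document gives nothing from which to quantify what remains.

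**The case against.** A reader might infer that the models contain nothing but arm, time and their interaction, and that the placebo comparison as a whole ignores baseline and strata. The text does not support that. It lists effects to be studied and does not exclude others. The preceding paragraph plans ANCOVA on baseline, with the main score as its example, and foresees mixed models whose covariates include the stratification parameters. It is not expressly confined to a single visit. If V0 is a level of time, the baseline score is in the model as a response. A further tempting claim, that omitting the strata necessarily inflates the standard error, fails for the V4 minus V0 contrast, as shown above.

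It is also fair that a journal article may leave covariate lists to the analysis plan, that rho = 0.5 is where adjustment gains most over the better of the two unadjusted forms, and that the 12-point gain at that value ignores the entry cut-off.

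These objections narrow the point but do not remove it. The article gives the longitudinal model its own fixed and random effects, so this is more than silence. No wording carries the earlier adjustment across, and that adjustment is itself optional. With V0 as a free response, baseline is present but not used efficiently.

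**Conclusion.** The point holds in limited form. As listed, the longitudinal models give a week-16 arm difference with about 1.1 to 1.5 times the adjusted variance if V0 is a free response, or 1.1 to 2.8 times if V0 is left out. This rests on assumed correlations of 0.3 to 0.8, equal correlation between visits and complete data. For the QLQ-CIPN20 sensory score the excess is smaller because of the entry rule: about 6 to 8 power points at correlation 0.5 under the assumed SD, means and difference. Strata main effects add precision only when V0 is not a free response, by an amount that the document does not allow to be computed.

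The consequence is modest. The analyses are secondary and exploratory, the rule of 7 responders in 33 is untouched, and the article already lists the secondary status of the placebo comparison as a limitation. The reason to act is that the gain is almost free and that pre-specification removes discretion over covariates.

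**What to change.** In the paragraph on repeated data, state that:

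1. the longitudinal models include the baseline value of the outcome, either as a covariate with a baseline x time term and V0 removed from the outcome vector, or by keeping V0 in the outcome vector with a common mean across arms;
2. the three stratification factors enter as pre-specified main effects, not chosen from univariate results;
3. the week-16 arm difference from this model is the main between-arm estimate, still labelled secondary and exploratory.

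For the generalized linear version on responder status, use the continuous baseline sensory score and the strata in the same way.

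The cost is wording and a few degrees of freedom. Some strata may be sparse with 80 patients, which is why main effects without interactions among the factors are enough. The data are already collected and trial conduct does not change.

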### Statistical considerations

#### Sample size estimation

Fleming’s one-stage design will be used for sample size estimation. Sixty-six evaluable patients (33 by arm) will be accrued. The null hypothesis that the responder rate is 10% (maximal non-efficacy threshold, according to Smith et al*.* [43]) will be assessed against a one-sided alternative for the donepezil arm. The null hypothesis will be rejected if 7 assessable or more responders are observed in the 33 patients of the donepezil arm. This design yields a type I error rate of 0.0417 and a power of 91% for a responder rate of at least 30% in the donepezil arm (minimal clinical efficacy threshold). Thus, we have decided to include a total of 80 patients (2 × 40) to take into account lost to follow-up (20%, according to clinical practice with Alzheimer patients, which mainly corresponds to a poor tolerance at 5 mg/day dosage or when switching from 5 mg/day to 10 mg/day dosage), and possible tumor recurrence.

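### The missing-data check is tied to significant results, and its worst-case scenario is the least favourable one for the single-arm primary endpoint but not for the secondary comparison with placebo

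*Protocol article*

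**What the plan says.** The last part of the Statistical analysis section introduces missing data in these words: "to put significant results in perspective, a sensitivity analysis will be conducted to measure the impact of the missing data". It goes on: "A worst-case scenario will be defined as one where patients with missing data do not react to the treatment (whatever the treatment may be"). One rule therefore applies to both arms. A further step follows: "Additional analyses will then be performed according to the statistical nature of missing data (missing at random or not"), with multiple imputation or methods for repeated data named as options.

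The primary endpoint is the responder rate in the donepezil arm alone, analysed in patients who completed 16 weeks of treatment. The responder comparison with placebo is secondary, is done in both the intention-to-treat and per-protocol populations, and is declared exploratory. The sample-size section expects about 20% loss, put down mainly to poor tolerance at the 5 mg/day dose or at the step to 10 mg/day.

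**The concern.** Two things in this text are fixed badly.

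First, the stated purpose of the check is to qualify significant results. Nothing in the section plans it for a non-significant one, and the imputation analyses are worded as a step that comes afterwards, so they appear to hang on the same trigger. The trial exists to decide whether to proceed to phase 3. Missing patients can push that decision in either direction, and whether robustness is examined should not depend on the p-value.

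Second, the label does not fit the between-arm contrast. For one arm, counting missing patients as non-responders gives the lowest possible rate. For a difference between arms, the least favourable case for donepezil is that its missing patients did not respond and the missing placebo patients did. A reader told that a significant difference survived a worst-case analysis would think it sturdier than has been shown. The Discussion says that the placebo comparison, though secondary, will add to the level of evidence, so its robustness check should be correctly described.

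**Working it through.** **Inputs from the protocol article.** Sample size estimation: "The null hypothesis that the responder rate is 10% (maximal non-efficacy threshold"); "The null hypothesis will be rejected if 7 assessable or more responders are observed in the 33 patients of the donepezil arm"; "type I error rate of 0.0417 and a power of 91% for a responder rate of at least 30"%; "we have decided to include a total of 80 patients (2 × 40"). Expected loss is 20%, which is 0.20 × 40 = 8 patients per arm if it is equal.

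**Assumptions.** The article gives neither a placebo response rate nor a split of missing patients between arms. The counts below are illustrations. Patients outside the completer set are treated as missing.

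**1. The plan's own figure.** Exact binomial, reject at 7 or more of 33: P(X ≥ 7 | 10%) = 0.0417 and P(X ≥ 7 | 30%) = 0.906. Both match the stated design.

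**2. Primary endpoint, missing counted as non-response.** This leaves the numerator alone and raises the denominator, so it can only lower the rate. With 40 analysed, one-sided exact p against 10% is 0.0995 for 7/40 and 0.0419 for 8/40, so 8 responders would be needed. Here the scenario really is the worst case. For the same reason it can never rescue a negative result: 6/32 (p = 0.094) becomes 6/40 (p = 0.206). Only imputation could inform that case. Applying the completer rate to the 8 missing gives 6/32 × 40 = 7.5 responders of 40, which lies between 7/40 (p = 0.0995, still negative) and 8/40 (p = 0.042, positive). Such a result is close enough to the boundary that one would want to see the imputation, but the example does not show that the decision would change.

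**3. Placebo comparison, equal loss (8 per arm), Fisher exact, two-sided.**

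| Handling of missing patients | Donepezil | Placebo | Difference | p |
|---|---|---|---|---|
| Completers | 12/32 | 4/32 | +25.0 points | 0.041 |
| Stated rule: non-response in both arms | 12/40 | 4/40 | +20.0 points | 0.048 |
| Missing donepezil non-response, missing placebo response | 12/40 | 12/40 | 0 | 1.0 |

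A larger effect behaves in the same way. 13/32 versus 3/32 gives 13/40 versus 3/40 under the stated rule (+25.0 points, p = 0.010) and 13/40 versus 11/40 under the opposite imputation (+5.0 points, p = 0.81).

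**4. Direction under unequal loss.** Let r be the completer response rate and m the fraction missing, with D for donepezil and P for placebo. The stated rule replaces each r by r(1 − m). Therefore:
- relative risk is multiplied by (1 − mD)/(1 − mP);
- risk difference changes by rP·mP − rD·mD.

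The relative risk moves in donepezil's favour only if placebo has more missing data, and the risk difference only if rP·mP exceeds rD·mD.

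- More loss on placebo (2 versus 10 missing): 12/38 versus 4/30 (relative risk 2.37, difference 18.2 points, p = 0.092) becomes 12/40 versus 4/40 (relative risk 2.37 × 0.95/0.75 = 3.0, difference 20.0 points, p = 0.048).
- More loss on donepezil (10 versus 2 missing): 12/30 versus 4/38 (relative risk 3.8, p = 0.008) becomes 12/40 versus 4/40 (relative risk 3.8 × 0.75/0.95 = 3.0, p = 0.048).

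**The case against.** The article does not say that the check is confined to significant results; it states a purpose, and the sentences on the worst case and on further analyses carry no condition of their own. That is fair. The restriction is the plain reading, not an explicit rule, and a clarifying sentence would settle it. For the non-response scenario on the primary endpoint, the focus on positive results is also logical, since that scenario cannot overturn a negative one. The point about the trigger therefore bears on the imputation step and on the placebo comparison.

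A reader might infer that the rule tilts the trial towards donepezil. The document does not support that. It expects losses mainly from poor tolerance at the study doses, which would fall on donepezil, and the rule is then conservative. One might argue that placebo could lose more because patients whose analgesic treatment changes can be withdrawn from analysis. But withdrawal from analysis is not the same as missing data, secondary comparisons are also run by intention to treat, and the end-of-treatment visit with QLQ-CIPN20 is held after early discontinuation too. In the 12/38 versus 4/30 example the completer result is not significant, so on the plain reading the check would not be triggered. The risk difference there also moves by less than 2 points.

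A reader might also infer that the plan offers this scenario as its limit on the effect of missing data and leaves every conclusion unprotected. It does not: the scenario is openly defined, and multiple imputation or repeated-data methods follow. Finally, the placebo comparison is exploratory, and the Discussion says that a later trial must confirm it. All of this limits the weight of the point. The label is still wrong for the between-arm contrast, and the trigger still needs rewording.

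**Conclusion.** The point holds as a minor, worthwhile improvement. On its plain reading, the text plans missing-data sensitivity analyses for significant results and none for others. Its worst case is correctly named for the single-arm primary endpoint but not for donepezil versus placebo. With equal loss of 8 per arm, a difference that survives the stated rule at p = 0.048 falls to zero under the opposite imputation. The counts are illustrative, because the placebo rate and the split of losses are not given. The rule favours donepezil on the relative-risk scale only if placebo has more missing data, which is not what the sample-size section suggests. The design figures (0.0417 and 91%) are unaffected.

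**What to change.** In the Statistical analysis section:

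1. State that the planned missing-data analyses, including multiple imputation or the repeated-data methods, will be run for the primary endpoint and for the placebo comparisons whatever the p-value.
2. Rename the present scenario non-responder imputation. It may still be described as the worst case for the single-arm primary endpoint.
3. For the between-arm responder comparison, add either a scenario with missing donepezil patients as non-responders and missing placebo patients as responders, or a two-way tipping-point table that varies the assumed number of responders among the missing in each arm.

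The cost is a little more analysis and no new data. A significant difference from placebo may look less robust than it would under the present wording.
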